## Methods

### Study Design

#### Overall Study Design

This study is an unblinded, open-label, parallel-group randomized controlled trial evaluating the effect of a plant-focused diet on the nutritional status of malnourished patients undergoing PD. This study will be conducted over 6 months, alongside each participants’ routine PD clinic visits. Patients and the public were not involved in the design, conduct, reporting, or dissemination plans of this study.

#### Research Flow

This study protocol is adapted from a similar ongoing clinical trial involving patients with CKD with diabetes mellitus in the United States [16]. Figure 1 shows a diagram outlining the research flow. The study begins with participant screening, recruitment, and baseline assessment conducted on the same day. Following baseline assessment, participants are then randomized into either the intervention group receiving a plant-focused dietary intervention or the control group receiving a standard renal dietary intervention.

A 2-week familiarization phase is implemented immediately after randomization as part of the intervention period. During this phase, participants begin following their assigned dietary intervention and receive additional guidance and closer monitoring to support early adaptation and adherence. This phase is intended to facilitate understanding of the dietary protocol and to identify and address potential challenges early, rather than to assess eligibility or introduce selection bias.

Participants from both groups are instructed to continue the assigned dietary intervention for 6 months. Key outcome assessments are conducted at baseline (0 months), midpoint (3 months), and end line (6 months). Data collected will be analyzed for subsequent report writing and publication.

The intervention and study procedures, including screening, recruitment, data collection, and intervention delivery, will be conducted by a registered dietitian. Health care staff at the study site will assist with clinical procedures such as blood collection.

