### Research Objectives

The primary objective is to determine the effect of a plant-focused dietary intervention on changes in serum albumin from baseline to 6 months compared with standard-of-care renal diet in malnourished patients undergoing PD.

The secondary objectives are (1) to determine the effect of a plant-focused dietary intervention on changes in anthropometric measurements (BMI, TSF, and MAMC), biochemical and inflammatory markers (lipid profile, hs-CRP, and renal parameters), dietary adequacy and nutrient intake, MIS scores, physical function and muscle strength, QOL, appetite scores, and dialysis adequacy from baseline to 6 months compared with standard-of-care renal diet in malnourished patients undergoing PD and (2) to determine the baseline nutritional status of malnourished patients undergoing PD, including their knowledge, attitude, and practices of renal diet intake, as well as sociodemographic characteristics and medical history.

Exploratory objectives are to assess adherence to a plant-focused dietary intervention over the 6-month period and to evaluate retention rates over 6 months of intervention.

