#### Dietary Assessment and Compliance Toward Diet Regime

Participants will complete a 3-day food diary monthly (2 weekdays and 1 weekend). At the first clinic visit, participants will receive training on how to accurately record only foods and beverages consumed using household measurements and a colored food album to assist with portion size estimation. Dietary intake data will then be analyzed using Nutritionist Pro (version 5.1.0; Axxya Systems [22]) using information from the Nutrient Composition of Malaysian Foods and Singapore Food Composition Book (Ministry of Health Singapore [23,24]).

Dietary adherence will be evaluated using a binary compliance scoring system, as detailed in Tables 2 and 3. Although arbitrarily set, the scoring categories were informed by clinical relevance, current dietary guidelines (medical nutrition therapy and Kidney Disease Outcomes Quality Initiative), and prior literature on compliance assessment in chronic disease populations [7,21,25].

**Table 2 table2:** Dietary compliance scoring system (scored per day).

Category				Scoring criteria^a^		
				Score=0		Score=1

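### The one-day baseline, the 3-day food diary first taught at that visit, and Table 1's food-record schedule cannot all be met; if randomization is on the same day, the baseline diary is kept on the assigned diet

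*Protocol article*

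**What the plan says.** Research Flow describes the start of the trial in one sequence. "The study begins with participant screening, recruitment, and baseline assessment conducted on the same day". Then: "Following baseline assessment, participants are then randomized into either the intervention group" or the control group. Then: "A 2-week familiarization phase is implemented immediately after randomization as part of the intervention period". In that phase "participants begin following their assigned dietary intervention and receive additional guidance and closer monitoring".

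Under Dietary Assessment and Compliance Toward Diet Regime, intake is measured by diary: "Participants will complete a 3-day food diary monthly (2 weekdays and 1 weekend" day). Training comes with the visit: "At the first clinic visit, participants will receive training on how to accurately record only foods and beverages consumed".

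Four other places bear on timing:
- Participant Screening and Recruitment describes only a short explanatory telephone call before the visit.
- Informed Consent requires consent before any study procedure.
- Table 1 has separate Screening and Month 0 columns and ticks food records in both, as well as at Months 3 and 6.
- Intervention Group vs Control Group gives both arms individual dietary counseling at the baseline data collection point.

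Research Objectives lists, among the secondary objectives, change in "dietary adequacy and nutrient intake, MIS scores, physical function and muscle strength, QOL, appetite scores, and dialysis adequacy from baseline to 6 months". Table 4 assigns dietary adequacy to a repeated-measures model with a time-by-group interaction.

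**The concern.** A diary that spans three days, and that participants learn to keep only at the visit, cannot be part of a baseline assessment completed at that visit. The protocol describes no run-in, no diary before the visit, no dietary recall, and no interval between visit and randomization in which the diary could be kept.

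The order of events therefore matters. If participants are randomized and counseled that day, the record labeled baseline describes their first days on the assigned diet. A time-by-group contrast then measures change from an early on-treatment value instead of from intake before treatment. The arms could also differ at baseline because of treatment, which randomization is meant to rule out. Intake before the diet cannot be recorded by diary once the diet has started, so the problem is easier to prevent than to repair.

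**Working it through.** **The plan's own figure.** The only calculation in the plan is the sample size for serum albumin: n per group = 2 × (1.96 + 0.84)² × 5² / 3² = 43.56, rounded up to 44. With 10% dropout, 44 / 0.9 = 48.9, so 49, which the plan rounds to 50. It reproduces, and diary timing does not affect it.

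**When can the baseline diary be finished?** Inputs: two weekdays and one weekend day; training at the first visit; consent before study procedures. Assumptions: a clinic visit from Monday to Friday, with recording from the next day.

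| Visit day | Earliest qualifying days | Complete on |
|---|---|---|
| Monday | Tue, Wed, Sat | day +5 |
| Tuesday | Wed, Thu, Sat | day +4 |
| Wednesday | Thu, Fri, Sat | day +3 |
| Thursday | Fri, Sat, Mon | day +4 |
| Friday | Sat, Mon, Tue | day +4 |

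Even if the visit day itself were counted, three separate days cannot end before day +2. The diary is never complete on the baseline day. Two such records, one for Screening and one for Month 0, fit still less.

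**The two possible readings.**
- *Randomization on the visit day.* The diet starts that day, and the earliest possible baseline diary (day +1 to day +5) lies inside the 2-week familiarization phase. The record is on treatment.
- *Randomization after the diary is returned.* The dietary baseline is sound, but baseline assessment is then not finished on the screening day, and the sentence in Research Flow is wrong.

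Either way, some text has to change. The first reading fits the article somewhat better: the flow is one continuous sequence, Table 1 has no randomization visit, and counseling is placed at baseline. None of this states the day.

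**Effect on the contrast under the first reading.** Let D0 be the expected between-arm difference in the baseline diary and D6 that at 6 months. The change contrast estimates D6 − D0. With a pre-treatment diary, D0 is zero in expectation and the contrast equals D6. With an on-treatment diary, D0 is unknown:
- If D0 has the same sign as D6 and is smaller, the contrast shrinks toward zero.
- If adherence is highest under the closer early monitoring and then fades, D0 can exceed D6 and the contrast changes sign.
- If both arms respond equally at first, as could happen for energy or protein, D0 is zero and there is no bias.

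The document gives no value for D0, so neither size nor direction follows from it.

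**The case against.** The strongest reply is that the protocol never says randomization is on the visit day. The same-day sentence covers screening, recruitment and baseline assessment only. Randomization comes after baseline assessment, and since food records are part of Month 0, the stated order puts them first. The word immediately ties the diet to randomization, not randomization to the visit. The flowchart (Figure 1), which might settle the matter, is not available here. Food records ticked at Screening also suggest that a dietary measure before randomization was intended.

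This stands, and it limits the point. A reader might infer that the diary can only be kept after randomization, or that the dietary objective has no true baseline. The document supports those statements only if randomization is on the visit day. A reader might also infer a bias toward zero, or attach a percentage to it; neither can be derived.

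It is also correct that intake at 3 and 6 months can still be compared between arms as randomized. Nor can harm to the planned cross-sectional paper or to the adjustment for baseline nutritional status be assumed, because neither is said to use diary intake.

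The reply does not remove the conflict. Even if randomization waits, a same-day baseline cannot contain this diary, and no window for keeping it is described. That is a contradiction between stated elements, not detail left to a fuller document.

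**Conclusion.** The point holds as an internal contradiction with a conditional consequence. The one-day baseline in Research Flow, the 3-day diary first taught at the first visit, and the food-record ticks at Screening and Month 0 in Table 1 cannot all be met. The shortfall is at least 3 to 5 days under the calendar assumptions above.

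If randomization is on the visit day, the time-by-group test for diary-based intake does not measure change from a pre-treatment baseline. That rests on an inference about the day of randomization, and the bias has no derivable size or direction.

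The reach is limited to diary-based secondary outcomes. Serum albumin and other measures that can be completed in a single visit before randomization are not affected. The matter deserves correction soon, but it does not put the primary analysis at risk.

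**What to change.** Reconcile Research Flow, Table 1 and the dietary assessment section, and state when the baseline diary is kept relative to randomization and the start of the diet. In practice:

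1. At the screening visit, obtain consent and give diary training.
2. At a separate Month 0 visit, collect the completed 3-day diary and do the remaining baseline measures.
3. Only then randomize and give arm-specific counseling and meal plans.
4. Use one 3-day diary for the dietary baseline, and say what the Screening tick for food records means or remove it.

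This gives Table 1's two columns separate visits. Replacing the baseline diary with a recall is not recommended unless the same instrument is used at follow-up, because otherwise the method changes between time points.

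For participants already enrolled (9 of 100 at submission), flag any baseline diary dated after randomization and do not use it as a baseline value. Their intake at 3 and 6 months can still enter a comparison between arms at those times.

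The cost is a protocol amendment, about a week's delay before randomization and one extra contact per participant. No additional participants are needed. At the submission count, 100 − 9 = 91 participants were still to be recruited, so an early change protects most of the sample.

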**Figure 1 figure1:**
[figure not shown]
Research flowchart.

### Recruitment

#### Study Population

Participants will be recruited from the nephrology unit at a tertiary care hospital in Klang, following approval from the research ethics committee. A second center may be considered to meet recruitment targets.

#### Sample Size

The sample size was calculated using the standard formula for comparing 2 independent means in a parallel-group design using several assumptions.

On the basis of previous studies in dialysis populations, an estimated SD of 5 g/L was used to account for heterogeneity and to avoid underestimation of sample size. Notably, studies by Kalantar-Zadeh et al [17] and Rambod et al [18] reported serum albumin SDs ranging from 1.9 to 4.4 g/L, while a study by Limwannata et al [19] reported an SD of 5.0 g/L.

A clinically meaningful difference (δ) of 3 g/L (0.3 g/dL) was selected as it is consistent with differences in serum albumin levels observed across dialysis populations in previous studies. For instance, variations of 0.3 to 0.4 g/dL are observed between cohorts reported in studies by Rambod et al [18] and Limwannata et al [19]. Additionally, serum albumin is a well-established predictor of morbidity and mortality in patients undergoing dialysis, and even modest changes are considered clinically relevant in reflecting improvements in nutritional status [17].

Using the formula mentioned below, a 2-sided significance level of.05 (Zα/2=1.96) and 80% power (Zβ=0.84) were used to calculate the sample size. As a result, a minimum of 44 participants per group was required. After accounting for an anticipated 10% dropout rate, the sample size was rounded up to 50 participants for each group, with a total sample size of 100 participants. As repeated measurements will be conducted at baseline, 3 months, and 6 months, the calculated sample size is considered conservative.

The sample size was calculated using the standard formula for comparing 2 independent means in a parallel-group design, as shown below:

[figure not shown]

Where n is the sample size per group, Zα*/*2 is the standard normal deviate for a 2-sided significance level (1.96 for *α*=.05), Zβ is the standard normal deviate for power (0.84 for 80% power), σ is the SD, and δ is the expected difference between groups.

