### Statistical Analysis

Statistical methods are detailed in Table 4. Data will be analyzed using SPSS (version 28; IBM Corp). Normality of continuous data will be tested using the Kolmogorov-Smirnov test.

**Table 4 table4:** Summary of the statistical analysis.

Study outcomes	Variables	Statistical analysis
Primary or main outcome	Serum albumin	GLM^a^-repeated measures (time×group interaction)
Secondary outcomes	Anthropometric data Biochemical data Dietary adequacy Physical function Quality of life Appetite and food satisfaction Dialysis adequacy	GLM-repeated measures (time×group interaction)
Exploratory or feasibility outcomes	Dietary adherence or compliance Retention rate	Descriptive statistics and chi-square test

^a^GLM: generalized linear model.

The primary analysis will evaluate changes in serum albumin from baseline to 3 and 6 months between intervention and control groups. A generalized linear model for repeated measures will be used to assess time, group, and interaction effects. Analyses will follow the intention-to-treat principle, with missing data handled using the last observation carried forward method. Adjustment for potential confounders such as age, sex, dialysis duration, and baseline nutritional status will be performed using multivariable models. Bonferroni correction will be applied for multiple comparisons. Secondary outcomes, including anthropometric, biochemical, dietary, MIS, physical function, QOL, appetite, and dialysis adequacy parameters, will be analyzed using similar repeated-measures approaches. Statistical significance will be set at *P*<.05.

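### The sample size rests on an SD of albumin levels while the primary endpoint is change from baseline; repeated measurement alone does not make it conservative, and baseline albumin is not named as a covariate

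*Protocol article*

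**What the plan says.** Under Sample Size, the article uses the formula for two independent means with a single SD. It says that "an estimated SD of 5 g/L was used to account for heterogeneity and to avoid underestimation of sample size". The support is that two earlier studies "reported serum albumin SDs ranging from 1.9 to 4.4 g/L" and that a third "reported an SD of 5.0 g/L". The target difference of 3 g/L is justified by differences in albumin levels between dialysis cohorts. The result is 44 per arm, raised to 50 for 10% dropout. The section then reasons that, since albumin is measured at baseline, 3 and 6 months, "the calculated sample size is considered conservative".

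Under Research Objectives, the primary objective concerns "changes in serum albumin from baseline to 6 months compared with standard-of-care renal diet". Under Statistical Analysis: "The primary analysis will evaluate changes in serum albumin from baseline to 3 and 6 months between intervention and control groups". Table 4 gives the primary test as the time-by-group interaction in a repeated-measures model. The same section adds: "Adjustment for potential confounders such as age, sex, dialysis duration, and baseline nutritional status will be performed using multivariable models". Baseline albumin is not named there.

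**The concern.** The variance behind the sample size and the variance of the endpoint are different quantities. When baseline is one of the time levels, a time-by-group interaction compares changes between the arms. The variance of a change is 2(1 − ρ) times the variance of a level, where ρ is the correlation between a patient's baseline and month-6 albumin. It is larger than the level variance whenever ρ is below 0.5. The article states no ρ, so the reader cannot tell whether the stated 80% power applies to the named endpoint.

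The claim that the size is conservative hides this gap. Repeated measurement can raise or lower precision for a change, depending on ρ and on when the effect appears. If ρ is modest and baseline albumin is not adjusted for, a null result could be read as coming from a trial with 80% power when it had clearly less.

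**Working it through.** **Inputs from the article:** difference δ = 3 g/L; SD 5 g/L; two-sided α 0.05 (z = 1.96); 80% power (z = 0.84); 1:1 allocation; 10% dropout; 50 per arm. **Assumed:** ρ, which the article does not give (range 0.2 to 0.6 shown), and the same SD at baseline and month 6. That 5 g/L is an SD of levels is read from the article's wording; the cited studies were not available.

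**1. The plan's own figure.** n = 2(1.96 + 0.84)² × 5² / 3² = 2 × 7.84 × 25 / 9 = 43.6, so 44 per arm. Then 44 / 0.9 = 48.9, so 49, which the article rounds up to 50. The figure is reproduced.

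**2. δ carries over; the SD does not.** Randomisation makes the expected baseline difference zero, so a 3 g/L difference in month-6 level is also a 3 g/L difference in change. Only the SD depends on the form of the analysis:
- unadjusted change: 5 × √(2(1 − ρ))
- month-6 albumin adjusted for baseline albumin: 5 × √(1 − ρ²)

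**3. Power for δ = 3 g/L** (noncentral t):

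| ρ | SD of change | Power, 44 per arm | Power, 50 per arm | Adjusted SD | Adjusted power, 44 per arm |
|---|---|---|---|---|---|
| 0.2 | 6.32 | 60% | 65% | 4.90 | 81% |
| 0.3 | 5.92 | 65% | 71% | 4.77 | 83% |
| 0.4 | 5.48 | 72% | 77% | 4.58 | 86% |
| 0.5 | 5.00 | 80% | 84% | 4.33 | 90% |
| 0.6 | 4.47 | 88% | 91% | 4.00 | 94% |

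At ρ = 0.3 the squared SD of change is 25 × 1.4 = 35, so the unadjusted change score needs 2 × 7.84 × 35 / 9 = 61 per arm before dropout, against 44.

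**4. Break-even correlation for 80% power, unadjusted change** (the plan's normal formula). The largest SD allowed is 3 × √(n/2) / 2.80.
- n = 44: 5.03 g/L, so ρ = 1 − 5.03² / 50 = 0.49, or about 0.50
- n = 50: 5.36 g/L, so ρ = 1 − 5.36² / 50 = 0.43
- With a level SD of 4.4 g/L, the same steps give 0.35 at 44 and 0.26 at 50 per arm.

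**5. The interaction test as planned.** This is the two-degree-of-freedom time-by-group test, assuming equal correlation between all visits, SD 5 g/L and 44 per arm:
- ρ = 0.5: about 82% if the full 3 g/L is present at month 3; about 70% if the difference is 1.5 g/L at month 3 and 3 g/L at month 6
- ρ = 0.3: about 67% and 54%

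The third visit therefore does not by itself secure 80%.

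**The case against.** The strongest reply is that the plan may already contain the remedy. It adjusts for baseline nutritional status, and the Objective and the Research Question measure nutritional status by serum albumin. If the covariate is baseline albumin, the residual SD is at most 5 g/L and the sizing stands at any ρ. This reply is plausible but not settled by the text. The term is one example in a list of potential confounders. The secondary objectives use the same term broadly, so the malnutrition inflammation score or BMI would also fit it. Table 4 lists the primary test without covariates.

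A second reply is that the inputs have slack. The SD of 5 g/L is the largest cited, and intention to treat with last observation carried forward would keep up to 50 per arm in the analysis. Both points stand, and they lower the break-even correlation as shown. They do not remove the dependence on ρ, and carried-forward early values may dilute an effect that is still developing.

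Three stronger readings might be inferred, and none is supported:
- That the stated power holds only if ρ is at least 0.5. This is true only for an unadjusted change score at about 44 to 45 per arm with SD 5 g/L.
- That entry at albumin below 40 g/L makes power worse by lowering ρ. Truncation also shrinks the baseline SD and the SD of change. Assuming an untruncated normal baseline with mean 36 and SD 5 g/L and an untruncated ρ of 0.5, ρ in the trial falls to 0.40, but the SD of change falls from 5.00 to 4.72 g/L and power at 45 per arm is 85%.
- That the endpoint must be redefined as a level. With baseline albumin as covariate, analysing the month-6 change or the month-6 level gives the same test of group.

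**Conclusion.** The point holds as a mismatch and an unsupported claim, not as a demonstrated shortage of patients. The SD is presented as one for levels, the endpoint is a change, no correlation is stated, and repeated measurement does not justify calling the size conservative. Whether power falls short depends on two things the article leaves open: ρ, and whether baseline albumin is a covariate. Without that covariate, an assumed ρ of 0.3 leaves about 65% to 71% power rather than 80%; at ρ of 0.5 or more the stated power is met or nearly so for the month-6 change. With the covariate, about 44 per arm suffices throughout. These figures assume an SD of 5 g/L at both visits and a true difference of 3 g/L. A reader might conclude that the trial is underpowered; nothing in the article shows that ρ is low, so that conclusion goes too far.

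**What to change.** - **Statistical Analysis and Table 4:** for the primary between-arm comparison of albumin at month 6, name baseline serum albumin as a covariate, in place of relying on the general term, and do not also enter it as an outcome time level. The endpoint may still be expressed as a change.
- **Sample Size:** remove the statement that the size is conservative. Say instead that 5 g/L is the SD of the albumin level and that the 80% power refers to the baseline-adjusted month-6 comparison.
- **If an unadjusted change score or time-by-group test is kept as primary:** state the assumed correlation, or an SD of change, and the resulting power.

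The cost is a few sentences. Baseline albumin is already collected and no patients are added. The article reports 9 participants recruited at submission, so the change can be made early.
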